## Discussion

6

### State-of-the-art

6.1

While there is growing recognition of the adverse effects of indoor and outdoor air pollution on children’s health, the specific role of the school environment has received comparatively less attention. Several studies have observed the adverse effects of air pollution exposure on cognitive development and cardiovascular health in children, yet limited studies have indicated the importance of air quality in schools to children’s health (6–8, 60, 61).

A prospective study conducted in Spain studied the impact of traffic-related air pollutants on the cognitive development in children aged 7–10 (9). Schools were classified into high- and low-pollution groups based on modeled nitrogen dioxide (NO₂) levels. The findings revealed a slower progression in cognitive development among children attending schools in higher pollution areas, emphasizing the critical need for effective air quality regulations in educational settings. More recently, a randomized, double-blinded crossover study in China (2024) demonstrated the cognitive benefits of indoor air filtration in college students (5). Researchers observed that a significant reduction in indoor air pollutant concentrations was followed by a corresponding increase in student test scores. These results suggest that even a short-term reduction of PM concentrations can significantly improve cognitive function. Given that children are inherently more vulnerable to these effects, the necessity of the present study is further underscored.

The association between PM_2.5_ exposure and BP in children was explored in several studies. In 2022, this association was observed in school children aged 9–10 at elementary schools in Korea (10). Notably, this study assessed both indoor and outdoor PM_2.5_ levels at children’s homes, classrooms, and surrounding outdoor environments. A significant relationship was observed between elevated PM_2.5_ exposure and increased BP, reinforcing the relevance of indoor exposures during school hours. A 2025 randomized crossover trial involving 79 children (average age: 10) in China also demonstrated the significant cardiovascular benefits of air purification (22). By installing air purifiers in both classrooms and bedrooms, researchers compared true intervention against a sham control. The results revealed a significant decrease in SBP alongside a substantial reduction in PM_2.5_ levels. While this study confirms the benefits of air purification in high-pollution environments, the LEARN study seeks to determine if these cardiovascular improvements persist in regions with different levels of ambient air pollution.

Traditionally, environmental monitoring is the primary approach to assess IAQ. However, this approach is costly, time-consuming, and labor-intensive. It reflects potential external exposure only and does not account for factors such as breathing rate and individual variations in susceptibility, which can lead to large uncertainties in extrapolating human health effects from air pollutant measurements (62). In contrast, human biomonitoring has unique advantages and is considered the “gold standard” (63) for assessing human exposure to environmental pollutants. Human biomonitoring is a method for assessing human internal exposure to chemicals by measuring the parent chemicals or their metabolites (namely biomarkers) in human specimens (64). It accounts for the presence of chemicals absorbed by the body through all pathways (e.g., inhalation, dermal, and ingestion) and multiple sources, thereby providing better information on the interrelationships between exposure, dose, and possible health effects (Figure 8) (24, 64).

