### Study setting and eligibility criteria

2.1

LEARN is a multicenter study with case study sites in three European countries: Belgium, Denmark, and Greece. The Belgian study population is recruited from the Flemish Region of Belgium, in the Flemish provinces of Limburg, Antwerp, and Flemish Brabant. For the Danish and Greek sites, recruitment focuses on primary schools in the municipality of Aarhus and in Thessaloniki, respectively.

According to geographical location (feasibility, deprivation, etc.), schools are contacted (mail, phone, video call) for participation. The principal completes a questionnaire providing a detailed description of the school’s infrastructure. Schools with an air filtration system and/or policies requiring windows to remain closed are excluded. Sufficient space should also be present in the classrooms to position the filtration devices optimally, with at least 30 cm of clearance around them, to ensure effective intervention. For reasons of generalizability and external validity, we intentionally avoid imposing additional restrictive exclusion criteria. This approach ensures that the study remains representative of the real-life school environments where such interventions would be implemented.

Any primary school located in the included regions of Belgium, Denmark, or Greece complying with these criteria can participate, provided that at least two classes from the same school from the 4th, 5th, and/or 6th grade agree to take part in the study. Once the classes are confirmed, an information session is organized with the principal, teachers, parents, and students. During this session, the study is explained to the students in an age-appropriate manner. Additionally, each child receives an envelope containing detailed information about the study and a consent form for their legal guardian(s) to sign. Insufficient knowledge of the Dutch, Danish, or Greek language by the child or the child’s guardian(s) leads to exclusion from the study, due to the availability of study materials limited to these languages.

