### Sample size calculation

2.2

A linear mixed-effects model will be applied to evaluate the association between the IAQ, the intervention, and the measured clinical parameters and biological biomarkers. Random intercepts will be specified for school, class, and child, and site-specific estimates will be combined through meta-analysis. As no pilot data were available across all sites, a simulation-based power analysis was conducted in R. The simulations assumed a within-person residual standard deviation (SD) of 1, and intra-class correlations (ICCs) of 0.05 for school, 0.10 for class, and 0.50 for child. For each scenario, 1,000 datasets were generated. In each dataset, the group × time contrast at the final time point was estimated using a linear mixed model, and site-specific results were combined via random-effects meta-analysis. The proportion of simulations yielding a two-sided *p* < 0.05 was recorded. Results indicated that recruiting approximately 150 children per country would provide 90% power to detect a medium-sized standardized intervention effect (Cohen’s d = 0.5 SD). This medium effect was selected as a pragmatic benchmark and should not be interpreted as the minimum clinically important difference for each outcome. We acknowledge that smaller effects than d = 0.5 SD may still be clinically or public-health relevant, but our study may have limited power to detect such smaller effects, and null findings should therefore be interpreted with caution.

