**Figure 2 fig2:**
[figure not shown]
Schematic overview of the OurAir SQ 1750 mobile air purification system.

Prior to the study, a simulation was performed to determine the optimal placement and operating point of the air purifier in the classroom. The optimum was defined as an air-cleaning rate corresponding to six air changes per hour (ACH). This 6-ACH target is applied by adjusting the device setting to the specific volume of each participating classroom. For the initial pilot study, however, the device was deliberately operated at the maximum airflow setting (1885.9 m^3^/h) to assess performance under worst-case conditions; this setting still resulted in a tolerable noise level (45.7 dB(A)).

To ensure effective blinding, the sham-intervention classroom has a mobile air purifier with the main filter and activated carbon prefilter removed. This device mirrors the operating noise of the functional units in the intervention classroom, neutralizing sound as a potential confounding variable (30).

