**Figure 8 fig8:**
[figure not shown]
Rationale for using biomarkers to assess risk (adapted from Louro et al.) (64).

The LEARN project wants to fill these research gaps through a comprehensive approach that includes the assessment of the air quality in the classrooms, the investigation of internal exposure via biomonitoring strategies, and the implementation of an intervention trial. It is an innovative study to characterize IAQ in classrooms and its impact on children’s health and well-being. As part of the LEARN project, this study develops and implements an integrated approach to understand the relationship between indoor air exposure at school, internal exposure of biomarkers, and cognitive outcomes of schoolchildren, and to introduce and evaluate novel remediation strategies in schools.

While previous research has established that air purifiers can improve children’s cognitive performance and blood pressure in specific settings, it remains to be seen how these benefits translate across varying levels of air pollution. By conducting our research across Belgium, Denmark, and Greece, we specifically account for the regional variations and environmental factors that influence the degree to which students actually benefit from these interventions.

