Additionally, although standardized procedures are implemented across all participating countries, some environmental monitoring strategies and measurements vary between sites due to local resource constraints or ethical limitations. This heterogeneity across study sites represents a limitation that could affect data comparability. To minimize this bias, we established strict standardized guidelines for data harmonization and will utilize appropriate statistical modeling to mathematically account for and evaluate between-country differences.

Furthermore, although children spend a significant portion of their time in classrooms, they are also exposed to various pollutants outside of school hours. While we estimate their overall exposure based on their home address, we are unable to account for time spent at other locations, such as during extracurricular activities or hobbies. We also could not account for traffic-related pollution during school commutes.

A final limitation of this study is the high participant burden associated with the intensive testing regimen and repeated cognitive sessions, which could introduce fatigue or boredom effects. However, this risk is mitigated by our highly structured scheduling designed to minimize missed school hours, the expertise of our pediatric-focused research team in keeping children comfortable, and strict adherence to participant autonomy, allowing children to opt out of tests at any point.

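### The question whether the blood pressure benefit persists at other ambient pollution levels rests on a confounded benchmark and on three country estimates; no stated analysis tests whether the purifier effect depends on pollution level

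*Protocol article*

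**What the plan says.** Section 6.1 (State-of-the-art) describes a randomized crossover trial in Chinese schoolchildren that found lower systolic pressure: "By installing air purifiers in both classrooms and bedrooms, researchers compared true intervention against a sham control". It places that result in a high-pollution setting and then gives LEARN's task: "the LEARN study seeks to determine if these cardiovascular improvements persist in regions with different levels of ambient air pollution". Later in the section the gap is put more generally, "it remains to be seen how these benefits translate across varying levels of air pollution", followed by the way LEARN is meant to fill it: "By conducting our research across Belgium, Denmark, and Greece, we specifically account for the regional variations and environmental factors" that influence how much students benefit.

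In LEARN the purifier stands in the classroom. Section 2.4 says "This 6-ACH target is applied by adjusting the device setting to the specific volume of each participating classroom", and no home unit is described. Section 6.2 lists as a limitation that "they are also exposed to various pollutants outside of school hours", without linking this to the earlier trial.

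On analysis, section 2.2 says "site-specific estimates will be combined through meta-analysis", and section 2.1 gives three countries. Section 5.3 enters classroom pollution and traffic exposure in the mixed models as adjustment variables. Section 3.2.2 makes environmental monitoring the primary exposure metric for pooled exposure-response analyses over all three countries. Pollutants are sampled in each classroom and outside each school (sections 3.1.3 and 3.1.4), and indoor particles are measured in the baseline period and in both intervention periods (section 3.1.5).

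**The concern.** Blood pressure is a primary outcome (section 4). If LEARN finds a small effect or none, section 6.1 invites the conclusion that purification helps only where ambient air is heavily polluted. Two things separate LEARN from the earlier trial, ambient level and the share of the day spent in filtered air, and the comparison cannot pull them apart.

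The second half of the question is internal to LEARN: does the benefit vary with pollution? That is effect modification. A meta-analysis of three country estimates gives an average and, at most, a contrast between countries that also differ in climate and school practice. A pollution covariate shifts the outcome level but leaves the purifier effect the same at every pollution level. An exposure-response analysis asks whether outcomes follow pollution, not whether the purifier does more in dirtier places.

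**Working it through.** **1. Comparison with the earlier trial.** The article gives 804 classroom hours per year as an OECD average (section 1). Assumptions, not in the documents: 175 to 190 school days per year, 9 hours per night in the bedroom, and bedroom units running all night. The article does not give the earlier trial's operating hours.

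- Classroom: 804/190 = 4.23 and 804/175 = 4.59 h per day. This fits the stated 31% of waking hours: 4.23/0.31 = 13.6 and 4.59/0.31 = 14.8 waking hours.
- Two-week period (336 h, 10 school days): 42 to 46 h filtered, or 13–14%.
- Adding bedrooms: 14 × 9 = 126 h more, so 168 to 172 h, or 50–51%.
- Ratio: 172/46 = 3.7 to 168/42 = 4.0.

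This only illustrates that the difference in filtered time could be large. The confounding itself needs no arithmetic.

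**2. Reproducing the stated 90% power (section 2.2).** Inputs: residual SD 1, d = 0.5, 150 children per country, group-by-time contrast, random-effects meta-analysis, two-sided 0.05. Assumptions: 75 children per sequence in each country and no true heterogeneity between countries.

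- Child, class and school intercepts cancel in a change score, whose variance is 2 × 1² = 2.
- SE per country = √(2 × 2/75) = 0.231.
- Three estimates combined by DerSimonian-Laird (200,000 simulated sets): power 91.0%, which agrees with 90%. A fixed-effect combination gives Φ(0.5/(0.231/√3) − 1.96) = 96.3%.

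The 90% therefore refers to the pooled average effect.

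**3. Country as the only moderator.** The SE of a difference between two countries is √2 times the country SE. The difference detectable with 80% power is (1.96 + 0.8416) times that. In residual SD units:

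| Contrast | Country SE | SE of difference | Detectable, 80% power | Power for effects 0.5 vs 0 |
|---|---|---|---|---|
| Group × time | 0.231 | 0.327 | 0.92 | 33% |
| Within-child crossover, √(2/150) | 0.115 | 0.163 | 0.46 | 87% |

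A heterogeneity test (Cochran Q) for effects of 0, 0.25 and 0.5 has 26% and 79% power, respectively. A trend over three equally spaced country levels, with estimated residual variance and one residual degree of freedom, has 10% and 19% power for a step of 0.25 SD. None of these tests separates pollution from whatever else differs between the countries.

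**4. Measured pollution as the moderator.** Take a pooled crossover model with 450 children, a within-child difference variance of 2 and a school-level modifier scaled to SD 1. The SE of the slope is √(2/450) = 0.067. The article does not give the number of schools, so 9 to 24 is assumed, with S − 2 degrees of freedom and no school-by-treatment variance.

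| Slope (SD per SD of pollution) | 9 schools | 15 schools | 24 schools |
|---|---|---|---|
| 0.10 | 25% | 28% | 30% |
| 0.15 | 49% | 55% | 58% |
| 0.25 | 89% | 93% | 95% |

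If country-specific intervention effects are also fitted, so that only within-country variation counts, the degrees of freedom fall to S − 4. The slope is then per within-country SD of pollution, and the ranges become 23–30% for 0.10 and 85–95% for 0.25.

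**The case against.** The quoted sentence stands in the Discussion. The aims in the Introduction and section 2 contain neither a moderation hypothesis nor a comparison with the earlier trial, and no between-trial analysis is planned. The article itself discloses the bedroom units. All of this stands and limits the weight of the point.

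A reader might infer that pollution enters LEARN only as three country labels, or that the question cannot be answered at all. The documents support neither. Pollution is measured in each classroom and outside each school, enters the models, and drives a planned exposure-response analysis. The sham-controlled crossover can estimate the effect of classroom filtration in each country and pooled. Section 6.2 also promises to evaluate between-country differences, and the within-child contrast has reasonable power for a large one.

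A reader might also blame test language or particle instruments for country differences in blood pressure. Test language bears on cognition only, and section 3.1.5 describes co-locating the devices before deployment to harmonise them.

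Finally, an interaction term is something that an unseen analysis plan may hold, so its absence alone would be no finding. The point rests on what the article does state: it names the three-country spread as its means of capturing how benefit varies, and that means is weak. No analysis plan can remove the confounding with bedroom filtration; only the wording can.

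**Conclusion.** The point holds in a limited form. A difference between LEARN and the classroom-plus-bedroom trial confounds ambient pollution with filtered time. Inside LEARN, the stated route to variation in the purifier effect is three country estimates, which detect only large differences (0.46 to 0.92 residual SD at 80% power, depending on the contrast) and cannot assign them to pollution. The stated uses of measured pollution do not test whether the purifier effect depends on its level.

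The power figures assume equal sequence sizes, the residual SD and sample size of section 2.2, and 9 to 24 schools. The 3.7- to 4.0-fold ratio of filtered hours rests on assumed school days and night hours and carries no weight beyond illustration. The main effect of classroom purification remains estimable. This is a matter of what may be concluded and of one missing secondary analysis, so it should be corrected but does not threaten the trial.

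**What to change.** - **Wording.** In section 6.1, state the blood pressure question as the effect of classroom-only purification in the three study regions. Add that a difference from the classroom-plus-bedroom trial will not be attributed to ambient pollution.
- **Analysis.** Pre-specify one secondary model with an intervention-by-pollution term. Pollution should be the pre-intervention level, continuous, at school or classroom level, with country-specific intervention effects so that the slope rests on variation within country. Use outdoor school measurements where available (sections 3.1.3 and 3.1.4), or baseline-period indoor particle levels (section 3.1.5). Label the latter as indoor, because they also reflect indoor sources and ventilation. Choose a measure that all three sites collect.
- **Reporting.** Give the purifier effect with its interval at a low and a high observed pollution level, in addition to the interaction p-value.

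The cost is a change of wording and one extra model term, with no new data. The drawback is imprecision: a modest slope will usually be missed, so the analysis should be labelled secondary and a null interaction should not be read as evidence that the effect is constant.

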**Figure 8 fig8:**
[figure not shown]
Rationale for using biomarkers to assess risk (adapted from Louro et al.) (64).

The LEARN project wants to fill these research gaps through a comprehensive approach that includes the assessment of the air quality in the classrooms, the investigation of internal exposure via biomonitoring strategies, and the implementation of an intervention trial. It is an innovative study to characterize IAQ in classrooms and its impact on children’s health and well-being. As part of the LEARN project, this study develops and implements an integrated approach to understand the relationship between indoor air exposure at school, internal exposure of biomarkers, and cognitive outcomes of schoolchildren, and to introduce and evaluate novel remediation strategies in schools.

While previous research has established that air purifiers can improve children’s cognitive performance and blood pressure in specific settings, it remains to be seen how these benefits translate across varying levels of air pollution. By conducting our research across Belgium, Denmark, and Greece, we specifically account for the regional variations and environmental factors that influence the degree to which students actually benefit from these interventions.

### Main strengths and weaknesses

6.2

The key strength of this study lies in its design. Comparing health outcomes, internal biomarkers, cognitive function, and well-being with IAQ before and after the application of a novel remediation strategy in a single-blinded crossover design allows for the precise determination of the effectiveness of the intervention. The crossover design also allows the same group of children to serve as their own controls, minimizing variability and providing a better understanding of the intervention’s health benefits. Due to the practical necessity of researchers installing the equipment, a single-blinded design was employed.

Another strength of this study is the carefully designed cognitive testing protocol. The potential for training effects was addressed by including two practice sessions during the BaP (57). Additionally, the use of standardized audio instructions ensures consistent delivery of test explanations across participants. Earlier studies often relied on oral explanations given by test administrators, which can introduce variability and potentially influence the results (65).

The same logic applies to the BP measurements. A baseline measurement is performed to allow children to become familiar with both the procedure and the researchers. During the BP assessments, five consecutive measurements are taken at each time point; the first two serve as internal acclimatization and will be excluded from the final analysis. This approach helps to minimize stress-related responses that can elevate BP readings during initial assessments (66). By addressing the acclimatization effect, the reliability of the blood pressure data is improved.

A third strength of this study is the modified standardized screening questionnaire with a scoring system. These questionnaires are given to and completed by the school staff responsible for each participating class. This enables easy identification of potential sources of indoor air pollutants in participating classrooms and ensures comparability between the two participating classrooms before the sampling campaign.

A fourth strength is the comprehensive environmental measurements, including VOCs and aldehydes, during the “Intervention Periods.” Unlike previous studies that only selected one approach for sampling duration, we perform continuous passive air sampling throughout the school hours, during the whole week (except weekends), in combination with active sampling 3 days per week during school hours. This design allows for the evaluation of overall and daily changes in levels of VOCs and aldehydes during each “Intervention Period,” and their potential relationships with classroom activities, weather, and other parameters. The dual sampling approach also allows us to avoid potential over- or underestimation of VOCs and aldehydes concentrations due to the inclusion of unoccupied periods in the sampling interval, as seen in previous studies (44, 67).

A fifth strength is that two urine samples are collected on Monday morning and Friday afternoon, respectively, to distinguish between school/home exposures. Monday’s samples are collected after being at home over the weekend to reflect primarily home-based exposure, whereas Friday’s samples are collected after 5 days of school (and at home in the evening) to reflect the integrated exposure at home and school. By comparing biomarker levels between the samples from these two time points, the effects of school-specific exposures and interventions can be more accurately assessed, minimizing confounding by home or out-of-school exposures.

On the other hand, there are also some limitations. A notable limitation is the exclusion of children and/or guardians with insufficient local language proficiency, which was logistically necessary to ensure the accurate completion of questionnaires and cognitive assessments. However, this criterion may introduce selection bias and limit the overall representativeness of the study population. Specifically, it potentially underrepresents certain vulnerable groups, such as children from recently immigrated families.

Additionally, although standardized procedures are implemented across all participating countries, some environmental monitoring strategies and measurements vary between sites due to local resource constraints or ethical limitations. This heterogeneity across study sites represents a limitation that could affect data comparability. To minimize this bias, we established strict standardized guidelines for data harmonization and will utilize appropriate statistical modeling to mathematically account for and evaluate between-country differences.

Furthermore, although children spend a significant portion of their time in classrooms, they are also exposed to various pollutants outside of school hours. While we estimate their overall exposure based on their home address, we are unable to account for time spent at other locations, such as during extracurricular activities or hobbies. We also could not account for traffic-related pollution during school commutes.

A final limitation of this study is the high participant burden associated with the intensive testing regimen and repeated cognitive sessions, which could introduce fatigue or boredom effects. However, this risk is mitigated by our highly structured scheduling designed to minimize missed school hours, the expertise of our pediatric-focused research team in keeping children comfortable, and strict adherence to participant autonomy, allowing children to opt out of tests at any point.

